### Data management and analysis

The data analysis will be done by using Stata software (version 11: StataCorp). Bivariate analysis such as Chi-square tests (for dichotomous and categorical variables), t test and ANOVA (for continuous and normally distributed variables) and Mann-Whitney-U test (for continuous variable with skewed distribution) will be applied to compare the two groups with respect of socio-demographic characteristics, number of clinic visits, practice of self-blood pressure monitoring, blood pressure at the time of enrolment, dietary intake, level of physical activity and fitness.

The primary outcome, change in systolic and diastolic blood pressure at six months and twelve months will be compared between and within the groups by using t test and ANOVA. If there are some differences in group characteristics, it will be adjusted by performing multivariate analysis of variance (MANOVA).

Since the secondary outcomes such as numbers of self-blood pressure monitoring, dietary intake, body composition (BMI, fat percentage, waist and hip circumference ratio), level of physical activity and physical fitness are also continuous variables, these will be examined as per primary outcome. The normality of the continuous variables will be checked before analysis and proper transformation will be done if the data is not normally distributed. The level of statistical significance will be set at p < 0.05.

In order to calculate nutrient intake, Nutritionist Pro™ Diet Analysis software will be used to analyse the diet record. It will focus mainly on energy, protein, fat, carbohydrate, sodium, dietary fibre and others. Based on the 7 days diet histories, the average energy consumed with macronutrients (e.g: Energy intake (kcal), protein (g), fat (g), saturated fat (g) and others) and micronutrients (e.g: calcium (mg), iron (mg), vitamins and minerals) value will be calculated. All nutrient intakes will be transferred to the Stata software for final data analysis.

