## Materials/design

### Objectives

Objectives of this study are to investigate the effect of lifestyle modification and peer support home blood pressure monitoring on blood pressure control, dietary intake, physical activity and fitness during asix-month intervention period. Moreover, we aim to assess whether these effects are sustained more than six months after the intervention has ended.

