### Sample size calculation and recruitment

The sample size was calculated by assuming p < 0.05 as the significance level, 80% power and 1 to 1 as the ratio of unexposed to expose in sample. The calculation was carried by using the OpenEpi version 2.3.1 [15]. On the assumption of an SD of 15 mmHg and 30% drop out, a sample size of 160 participants per group is required to detect the effect size of systolic blood pressure 5.4 mm Hg. The effect size used to calculate the sample size was based onthe result of a previous similar study[16].

Universal sampling method will be used to recruit the study participants. The 431 residents of the selected community housing complexes who were diagnosed as (stage 1 to 3) hypertension will be invited to the study. We will take all participants which fit with inclusion criteria and willing to participate to the study so that actual participants may be more than calculated sample size.

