### Intervention

The intervention is developed based on Social Cognitive Theory which includes social support, self-regulation and self-efficacy [17]. There will be three main components in the intervention i) Peer support for home blood pressure monitoring, ii) Face to face health coaching on healthy diet iii) Demonstration and training for indoor home based exercise activities.

Peer support groups, consisting of five persons per group will be formed based on the proximity of the residences. An Omron digital blood pressure monitor (HEM-7111) will be distributed to each group and participants will be trained by a state registered nurse on how to measure blood pressure and record the blood pressure reading in a log book.

Dietary assessments of individual participants will be conducted by three dietitians using 7 days diet histories. These dietitians will be randomly assigned to participant groups to assess the food intake. The same principal dietitian will conduct six sessions of health coaching to the participants in the group. The content of health coaching will include diet modification according to the DASH (Dietary Approaches to Stop Hypertension)diet [7,18] and reduction of sodium intake. The sodium reduction approach that will be used in this study is by educating the participants to use herbs and spices in their cooking and by reducing the table salt usage. Healthy cooking demonstration and practices of reading food label will also be included in the sessions of health coaching. High in sodium foods will be encouraged to be minimised. The health coaching materials to the intervention groups are the same whilst control will receive healthy diet leaflet at the beginning of the study. After completing the intervention, the three dietitians will do the post intervention dietary assessment using the 7 days diet histories.

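### With 30% dropout planned for, separate t tests and ANOVA of blood pressure change can drop partial follow-up and may bias the twelve-month (sustainability) comparison, in either direction

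*Protocol article*

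**What the plan says.** All references are to the protocol article.

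- **Sample size calculation and recruitment:** "On the assumption of an SD of 15 mmHg and 30% drop out, a sample size of 160 participants per group is required". The section does not say whether the 30% applies by six months, by twelve months or overall, nor how it splits by arm.
- **Data management and analysis:** the stated analysis of the primary outcome is that "change in systolic and diastolic blood pressure at six months and twelve months will be compared between and within the groups by using t test", with ANOVA also named. If group characteristics differ, "it will be adjusted by performing multivariate analysis of variance (MANOVA").
- **Objectives:** beyond the six-month effect, "we aim to assess whether these effects are sustained more than six months after the intervention has ended".
- **Study tools and measurements; Follow up and outcome measurement:** blood pressure is taken in both arms at baseline, six and twelve months.
- **Study design and setting; Intervention:** the trial is un-blinded, with four housing complexes allocated 1:1. The intervention arm has six coaching sessions, exercise training and log books. Controls receive a pamphlet and a BMI calculator.

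**The concern.** A t test of twelve-month change needs a baseline and a twelve-month value. Someone measured at baseline and six months and then lost adds nothing to it, although the six-month reading is in hand and says something about the missing one. The six-month test would still include that person, so the two contrasts need not describe the same people. MANOVA, in its usual form, drops anyone missing any outcome included in it.

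The second objective rests on reading the twelve-month effect against the six-month effect. Suppose intervention participants with little response leave after six months. The twelve-month test is then run in a favourable subset, and a flat effect can look as if it grows, or a vanished one as if it partly persists. If the selective loss is among controls, a sustained effect can look as if it fades. The unequal burden on the two arms makes loss that differs by arm and response plausible, though not certain.

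**Working it through.** **1. The plan's own figure.** Inputs from the sample size section: difference 5.4 mmHg, SD 15 mmHg, alpha 0.05 (two-sided assumed), power 80%, ratio 1:1.

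n per arm = 2 × [15 × (1.960 + 0.842) / 5.4]² = 121.1, so 122. Then 122 × 1.3 = 159, which matches the stated 160. The 30% loss is therefore built into the plan. (Dividing by 0.7 would give 175. That is a separate matter.)

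**2. Who enters each test.**
- If 30% miss each visit, 160 × 0.7 = 112 per arm are seen at each. The number seen at both ranges from 160 - 48 - 48 = 64 (no overlap in absences), through 160 × 0.49 = 78 (independent absences), to 112 (the same people absent twice).
- If 15% are lost by six months and 30% by twelve (assumed), 136 and 112 per arm are seen. The twelve-month test then ignores 136 - 112 = 24 six-month readings per arm.

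**3. Bias of an attender-only contrast.** Let d be the share missing in an arm, and D the mean change in attenders minus that in non-attenders. The attender mean differs from the full-arm mean by d × D, so

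bias = d_int × D_int - d_ctl × D_ctl.

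The documents give neither d by arm nor D, so all rows are assumptions:

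| d_int, d_ctl | D_int, D_ctl (mmHg) | Bias (mmHg) |
|---|---|---|
| 0.30, 0.30 | 0, 0 | 0 |
| 0.30, 0.30 | -5, -5 | 0 |
| 0.30, 0.30 | -3, 0 | -0.9 |
| 0.30, 0.30 | -5, 0 | -1.5 |
| 0.30, 0.30 | 0, -5 | +1.5 |
| 0.30, 0.15 | -5, -5 | -1.5 + 0.75 = -0.75 |

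The last row shows that acting equally means equal loss as well as equal selection.

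**4. Simulation of the twelve-month test.** Assumed: 160 per arm, SD 15 at each visit, correlation 0.6 between visits, true effect -5.4 mmHg at both follow-ups, 15% lost at random before six months, about 30% lost by twelve, clustering ignored. Later loss in the intervention arm depends on six-month change, with the log-odds shown per SD of change. That SD is 15 × √(2 × 0.4) = 13.4 mmHg.

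| Log-odds per SD | t test of twelve-month change | Likelihood analysis of all visits |
|---|---|---|
| 0 | -5.4 | -5.4 |
| 0.5 | -6.0 | about -5.4 |
| 1.0 | -6.7 | about -5.4 |
| 1.5 | -7.3 | about -5.4 |

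In these runs total loss in the affected arm rises with the dependence, to about 36% in the last row. A rerun that held it at 30% gave -6.0, -6.5 and -6.8 for the last three rows. The six-month test stays near -5.4 throughout.

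Variants:
- same dependence in both arms: -5.4;
- dependence in the control arm only: about -4.2;
- true twelve-month effect of zero, intervention-arm dependence: t test -1.3 (-0.9 to -1.4 in the rerun with loss held at 30%), likelihood analysis about 0.

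With unrelated loss the likelihood analysis is slightly more precise (SE 1.74 against 1.79).

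**The case against.** The strongest reply is that this is silence rather than error. The article names no analysis set and no missing-data method. It does not say that only attenders are analysed and does not rule out imputation before the tests. Such detail is commonly left to a full protocol or analysis plan, which is not shown. That stands against any claim of omission. It does not remove the point, which concerns a method the article does name for the primary outcome, set beside its own planned loss and its sustainability aim.

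Second, the word ANOVA is open. A repeated-measures ANOVA on long-format data with a participant term keeps people with partial follow-up. Under the same assumptions it gave -5.4, -5.4, -5.4 and -5.5. Run listwise on all visits, ANOVA or MANOVA would use the same people at both times. Both are fair, and so the point is conditional on separate tests by visit.

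Third, the shifts (0.6 to 1.9 mmHg) are about one standard error (1.79) or less. The simulated loss also depends only on observed six-month change, the setting that favours the proposed model. Both are true.

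A reader might also infer from the Intervention section ("After completing the intervention, the three dietitians will do the post intervention dietary assessment using the 7 days diet histories") that people who stop attending sessions would not be measured. The documents do not support this. The wording fixes timing and concerns diet, a secondary outcome, while the measurement and follow-up sections schedule both arms at six and twelve months without reference to attendance.

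**Conclusion.** The point holds in conditional form. If the named tests are run separately by visit on the data as collected, they discard usable follow-up, and the sustainability comparison may be biased. Under the assumed values, selective loss in the intervention arm alone turns -5.4 mmHg into about -6.0 to -7.3, and selective loss in the control arm alone into about -4.2. Size and direction depend on loss by arm and visit, which the article does not give. The figures are for systolic pressure; the same reasoning applies to diastolic.

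A reader might go further and conclude that the twelve-month result is biased, or that the two visits necessarily compare different people. Neither follows. Bias is zero when loss is random or acts equally in both arms, and the two samples coincide if the same people miss both visits. The change is still worth making: it is cheap, costs no precision when loss is unrelated to response, and protects a stated objective when loss depends on observed response in one arm.

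**What to change.** In Data management and analysis, make the primary analysis one longitudinal linear mixed model for each blood pressure outcome, using the baseline, six- and twelve-month readings. Include every enrolled participant by the allocation of their complex, whatever their session attendance. Take the arm-by-visit contrasts at six and twelve months as the primary estimates. Account for housing complex in a way suited to four clusters; a model with participant effects alone would overstate precision. Report loss by arm and visit.

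Cost: wording, and a standard model in the Stata software already named. No new visit, measurement or participant is needed. There are two downsides. The model assumes data are missing at random given the observed readings, so it does not remove bias from loss that depends on unobserved values. Accounting for the complexes will widen the intervals, since two complexes per arm leave only 4 - 2 = 2 degrees of freedom between complexes.

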**Methods:**

The study is a two armed, parallel group, un-blinded, cluster randomized controlled trial undertaken within lower income areas in Kuala Lumpur. Two housing complexes will be assigned to the intervention group and the other two housing complexes will be allocated in the control group. Based on power analysis, 320 participants will be recruited. The participants in the intervention group (n = 160) will undergo three main components in the intervention which are the peer support for home blood pressure monitoring, face to face health coaching on healthy diet and demonstration and training for indoor home based exercise activities while the control group will receive a pamphlet containing information on hypertension. The primary outcomes are systolic and diastolic blood pressure. Secondary outcome measures include practice of self-blood pressure monitoring, dietary intake, level of physical activity and physical fitness.

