### Study design and setting

The study is a two armed, parallel group, un-blinded, cluster randomized controlled trial undertaken within lower income areas in Kuala Lumpur. There are six community housing complexes in the study area. Of these four housing complexes will be randomly selected and allocated (1:1) to the intervention and control arm (Figure 1).

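### Four housing complexes are randomised, but the between-arm outcome tests ignore the complex, so they are anti-conservative for any positive intracluster correlation

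*Protocol article*

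**What the plan says.** The protocol article describes the design under Study design and setting: "The study is a two armed, parallel group, un-blinded, cluster randomized controlled trial undertaken within lower income areas in Kuala Lumpur". On the unit and number of clusters, the same section says "Of these four housing complexes will be randomly selected and allocated (1:1) to the intervention and control arm", and the abstract confirms two per arm: "Two housing complexes will be assigned to the intervention group and the other two housing complexes will be allocated in the control group".

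Data management and analysis names the primary method. Change in systolic and diastolic pressure at six and twelve months "will be compared between and within the groups by using t test and ANOVA". MANOVA is added only if the groups differ in their characteristics. Secondary outcomes are handled in the same way as the primary outcome, and significance is set at p < 0.05. The article mentions no ICC, random effect, robust variance or cluster-level summary.

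The sample size section is a per-participant calculation. It takes a standard deviation of 15 mmHg, allows for a loss of 30%, and concludes that "a sample size of 160 participants per group is required to detect the effect size of systolic blood pressure 5.4 mm Hg".

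The Intervention section adds a further level of grouping in one arm: "Peer support groups, consisting of five persons per group will be formed based on the proximity of the residences".

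**The concern.** When complexes are randomised, the error of the arm difference has two parts: variation between residents and variation between complexes. A t test or ANOVA on residents estimates only the first part. If residents of one complex resemble each other at all in how their blood pressure changes, the standard error is too small, the interval too narrow and the p value too low.

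The design makes some resemblance plausible. Peer groups are formed among neighbours and share one monitor, coaching is given in groups, and the Discussion counts on an existing social network in the community.

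At stake is whether a significant result, obtained exactly as planned, could be attributed to the intervention rather than to two pairs of complexes that happened to move differently. The article names the primary test, so this is a stated method that does not fit the stated design. It is not a detail left to an analysis plan.

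**Working it through.** **Inputs.** From the protocol article: 4 complexes, 2 per arm; SD 15 mmHg; difference 5.4 mmHg; 80% power; significance level 0.05; 30% dropout; 160 per group. Assumed here: a two-sided test, equal complexes, exactly 320 recruited, and ICC from 0.001 to 0.05.

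**Step 1: the plan's own sample size.** n = 2 × (1.96 + 0.84)² × 15² / 5.4² ≈ 121 to 122 per group by the normal or the t calculation. Taking 122, 122 × 1.30 = 159, which matches the stated 160. Dividing by 0.70 instead gives 175, which does not match. The stated figure is thus a calculation for independent participants, with a design effect of 1. This supports reading the t test as a test on residents.

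**Step 2: cluster size.** 320 × 0.70 / 4 = 56 completers per complex, 112 per arm.

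**Step 3: design effect and real type I error.** DE = 1 + (56 − 1) × ICC. The naive test rejects when the difference exceeds 1.96 naive standard errors, so its real error is 2 × [1 − Φ(1.96/√DE)].

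**Step 4: interval width.** Naive SE = 15 × √(2/112) = 2.00 mmHg, so the naive half-width is 1.96 × 2.00 = 3.9 mmHg. The half-width on 2 df is 4.30 × 2.00 × √DE (using the true SE; any one trial's interval will vary around this).

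| ICC (assumed) | DE | Real type I error | 95% half-width on 2 df, mmHg |
|---|---|---|---|
| 0.001 | 1.055 | 5.6% | 8.9 |
| 0.005 | 1.275 | 8.3% | 9.7 |
| 0.01 | 1.55 | 11.5% | 10.7 |
| 0.02 | 2.10 | 17.6% | 12.5 |
| 0.05 | 3.75 | 31% | 16.7 |

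A simulation of 100,000 trials per setting agrees: 5.6%, 8.2%, 11.7%, 17.8% and 31.4% for the naive test. A t test on the four complex means stays at about 5% throughout. With 80 analysed per complex the inflation is larger: 5.9%, 9.7%, 14.3%, 22.2% and 37.8%.

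**Step 5: what needs no ICC.** Four complex means in two arms leave 4 − 2 = 2 df, critical value 4.30. Choosing 2 of 4 complexes gives C(4,2) = 6 allocations, so the smallest two-sided randomisation p value is 2/6 = 0.33.

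**Step 6: power of the valid test.** From the non-central t on 2 df for 5.4 mmHg:
- 160 analysed per arm: 43% at ICC 0, 28% at 0.01, 22% at 0.02, 14% at 0.05.
- 112 analysed per arm: 33%, 24%, 20% and 14%.

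**Step 7: would a mixed model do instead?** The between-complex variance is estimated at zero when the mean square between complexes within arms falls below that within complexes. The probability is P[F(2, 220) < (1 − ICC)/DE], where 220 = 4 × 55. At ICC 0.005 the bound is 0.995/1.275 = 0.78 and the probability about 54%. At ICC 0.05 it is 0.95/3.75 = 0.25 and about 22%. In those trials the model drops the complex and, unless its df are fixed, returns to the naive test.

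**The case against.** The strongest objection concerns size. A reader might infer that the type I error is certainly well above 5%. The documents do not support that as a fact, because they give no ICC. At 0.001 the error is under 6%. The outcome is change in blood pressure, whose ICC may be lower than that of blood pressure level. This stands: the direction of the error is certain for any positive ICC, but its size is conditional.

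A reader might also infer that any difference between the complexes, for instance in ethnicity, income, clinic access or field staff, would pass for an intervention effect. The documents report no such differences. Analysing change removes stable differences in level, so only differences in trend or response would pass through. The planned MANOVA might adjust for measured characteristics, although it does nothing about clustering.

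The objection on scope also stands. The chi-square and Mann-Whitney tests sit largely in the descriptive comparison of groups, and the 2-versus-2 calculation does not apply to within-group comparisons. The point is confined to between-group outcome tests.

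Equal complexes of 56 are an assumption. The article invites 431 residents and allows for more than 320, so complexes may be larger or unequal.

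Finally, the article does not say that residents are the unit of analysis. But the sample size counts residents with a design effect of 1, and nothing points to a test on four means.

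**Conclusion.** The point holds for all between-group outcome comparisons. The planned test ignores the unit of randomisation and is anti-conservative whenever the ICC is above zero. Over an assumed ICC of 0.001 to 0.05, with 56 completers in each complex, the nominal 5% test has a real error of about 5.6% to 31%.

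These error rates do not depend on the SD. The interval widths do: they take the protocol's 15 mmHg as the SD of the analysed outcome, although the article does not say whether it refers to level or change. The 2 df and the smallest randomisation p value of 0.33 rest on no assumption beyond two complexes per arm. The p < 0.05 criterion therefore cannot be supported by the randomisation alone.

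**What to change.** In Data management and analysis, for all between-group outcome comparisons:

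- Replace the t test and ANOVA on residents with a t test on the four complex means of change, on 2 df. Make any baseline adjustment at participant level before averaging; a covariate at complex level would use up one of the two df.
- Keep a mixed model, if wanted, as a sensitivity analysis only, with between-complex df fixed at 2.
- Report the effect as an estimate with its cluster-based confidence interval, and state that p < 0.05 cannot be supported by the randomisation alone.

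The change is one of wording and needs no new data or staff. Its scientific cost is large and should be stated. The 95% half-width for systolic pressure goes from 3.9 mmHg to about 9 to 17 mmHg, against a target of 5.4 mmHg. Power is at most about 43% with 160 analysed per arm. The new analysis restores validity but not the stated 80% power, which would need more complexes. The study area has six; even a 3-versus-3 allocation gives C(6,3) = 20 arrangements and a smallest two-sided randomisation p value of 2/20 = 0.10.

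### The plan tests change in blood pressure within each arm as well as between arms, and does not say that only the between-arm contrast bears on efficacy

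*Protocol article*

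**What the plan says.** The analysis section of the protocol article (Data management and analysis) defines the variable as "The primary outcome, change in systolic and diastolic blood pressure at six months and twelve months" and says that it "will be compared between and within the groups by using t test and ANOVA". For self-monitoring counts, diet, body composition, activity and fitness, it says that "these will be examined as per primary outcome". One threshold covers all tests: "The level of statistical significance will be set at p < 0.05". Nothing labels the within-group results as descriptive, and nothing says which of the two comparisons decides whether the intervention worked.

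The Sample size section takes the other view of the question. It plans two groups in a 1:1 ratio and states that "a sample size of 160 participants per group is required to detect the effect size of systolic blood pressure 5.4 mm Hg", which is a between-group difference.

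**The concern.** A test of change inside one arm compares that arm with its own baseline, not with the control arm. It picks up whatever moves pressure over time: season, familiarity with being measured, changes in usual care and some regression to the mean. Some shared fall is plausible here. Controls receive a BMI calculator and a pamphlet on hypertension, diet and activity, and both arms are measured at baseline, six and twelve months.

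A significant fall in one arm and a non-significant fall in the other is not a test of the difference between them. If the two kinds of result sit side by side at the same threshold, a report could draw a favourable conclusion from the intervention arm's own change when the arms do not differ. That would give up what randomisation provides. The secondary outcomes carry the same exposure, because they inherit the same analysis.

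**Working it through.** **1. What the sample size rests on.** Inputs from Sample size calculation and recruitment: difference 5.4 mmHg, SD 15 mmHg, significance 0.05 (taken as two-sided, since sidedness is not stated), power 80%, ratio 1:1, drop-out 30%.

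- n per arm = 2 × SD² × (1.960 + 0.842)² / difference² = 2 × 225 × 7.85 / 29.16 ≈ 121.1, so 122.
- 122 × 1.30 = 158.6, so 159. This agrees with the stated 160 to within rounding.

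The planned size is thus that of a two-group comparison. With 30% loss, 160 × 0.70 = 112 per arm remain. I use 112 below. The choice of drop-out inflation is a separate matter.

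**2. What a within-arm test does when there is no treatment effect.** Assumptions: both arms truly fall by the same amount d, n = 112 per arm, SD of change s = 15 mmHg, two-sided 0.05 paired t test, arms independent, clustering ignored. The article gives an SD of 15 mmHg but does not say that it is an SD of change, and it gives no shared fall. Both are therefore assumptions, and I show a range.

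- Standard error = s/√n = 15/√112 = 1.417 mmHg.
- Noncentrality = d/1.417. Critical value of t on 111 df = 1.982.
- p = probability that noncentral t exceeds 1.982, which is a significant fall in the intervention arm.
- Probability of a significant fall in the intervention arm and not in the control arm = p(1 − p).

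| Shared fall d (mmHg) | d/1.417 | p | p(1 − p) |
|---|---|---|---|
| 0 | 0 | 2.5% | 2% |
| 1 | 0.71 | 10% | 9% |
| 2 | 1.41 | 29% | 20% |
| 3 | 2.12 | 56% | 25% |
| 4 | 2.82 | 80% | 16% |

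The last column drops again at 4 mmHg because the control arm is then usually significant too.

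**3. Sensitivity.** With 122 per arm, p is about 31%, 59% and 83% at 2, 3 and 4 mmHg. With a within-person correlation of 0.7, the SD of change is 15 × √0.6 = 11.6 mmHg. With 112 per arm, p is then about 44%, 77% and 95%.

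**4. The comparator.** Under the same assumptions a two-sided 0.05 between-arm test of change favours the intervention in 2.5% of trials whatever the size of the shared fall, because the fall cancels in the difference.

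**The case against.** The strongest case against is that the between-arm comparison is planned, is named first, and drives the sample size in a randomised parallel-group design. No sentence makes a within-arm p-value the basis for an efficacy conclusion. This stands. A reader might infer that the plan will declare efficacy from the intervention arm alone, or that it gives the two comparisons equal standing for that purpose. The text supports neither.

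A reader might also infer that a lasting effect will be judged by the intervention arm's own course from six to twelve months, because the Objectives ask "whether these effects are sustained more than six months after the intervention has ended" without naming a contrast. The article does not propose that. Both arms are measured at twelve months, and the between-group comparison is planned for that visit.

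The word within could instead mean the time factor of a repeated-measures ANOVA. That is possible, but the text names neither such a model nor a group-by-time test, and a time effect would not measure the treatment difference either.

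An article does condense a fuller plan. That excuses an omission. Here, however, a within-group comparison is positively assigned to the primary outcome.

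The size of the risk does depend on the shared fall, for which the article gives no figure. At no shared fall the within-arm test shows a significant fall in only 2.5% of trials, and at 1 mmHg in about 10%. Regression to the mean may be modest, because entry rests on an existing diagnosis.

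**Conclusion.** The point holds as a gap in how the stated analysis may be interpreted, for the primary and the secondary outcomes. If the shared fall is 2 to 4 mmHg and there is no treatment effect, a within-arm test in the intervention arm is significant in roughly 29% to 80% of trials, and the misleading one-arm-only pattern favours the intervention in 16% to 25%. These figures rest on 112 completers per arm, an SD of change of 15 mmHg, independent arms and no clustering. They describe what could follow from relying on within-arm results. They are not the false-positive rate of the between-arm test that is also planned.

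**What to change.** Add to Data management and analysis: conclusions on efficacy, for primary and secondary outcomes, at six and at twelve months, rest only on the between-arm difference, adjusted for the baseline value of the outcome. Within-arm changes are descriptive and are reported as means with confidence intervals.

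This is a change of wording. The baseline values are already collected, and the sample size already rests on the between-arm difference. The only loss is that within-arm p-values no longer support a conclusion. How the analysis should allow for the four housing complexes is a separate point with costs of its own, and this change does not settle it.
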